**Figure 1 f1:**
[figure not shown]
Hypothesized working mechanism of pamidronate in chronic nonbacterial osteitis (CNO). Legend: IV: Intravenous, Ly: Lymphocyte, Neu: Neutrophil, Pla: Plasma cell.

The theoretical efficacy of bisphosphonates in CNO is supported by observational data, showing how bisphosphonates, mainly intravenous pamidronate, lead to a reduction in pain and radiologic signs of disease activity in adults and children.^18^^-^^28^ Similar positive results were found in a first small randomized, double-blind, placebo-controlled *pilot* trial comparing pamidronate to placebo in 12 adult CNO patients.^29^ Adequately powered trials are essential to infer a causal relationship regarding the efficacy of pamidronate to reduce pain in CNO, elucidate the underlying mechanisms, gain deeper understanding of the optimal treatment regimen, gather information on safety, and identify predictors of therapy response. Hence, we conceptualized and launched an investigator-initiated RCT PAMidronate for pain in adult Chronic Nonbacterial Osteitis (PAM-CNO). The design and conduct of this RCT presents challenges, due to the rarity of the disease, the absence of a clear disease definition, and limited understanding of relevant outcome measures. We therefore report its protocol, including the methodological obstacles characteristic of doing research in rare and poorly defined diseases such as CNO.

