## Objectives

The primary objective of the PAM-CNO trial is to investigate the efficacy of intravenous pamidronate in reducing pain in adult CNO patients. Secondary objectives are to evaluate the effect of pamidronate on (1) a variety of patient-reported outcome measures (PROMs), (2) biochemical and immunological indices relevant to CNO, and (3) radiological parameters of disease activity and severity. Additional objectives are to evaluate baseline predictors of treatment response, to elucidate mechanisms by which pamidronate may reduce pain in CNO, and cost-effectiveness.

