## Materials and methods

### Trial setting and design

This is a single-center, superiority trial conducted at the Centre for Bone Quality of the Leiden University Medical Center (LUMC), which is the Dutch national expertise and referral center for CNO. The trial starts with a 6-mo double-blind, randomized, placebo-controlled phase with 1:1 allocation of pamidronate or placebo (see Figure 2). Double-blind placebo-control was deemed necessary to prevent reporting bias because the trial’s primary outcome is patient-reported pain, which is susceptible to a placebo-effect. The 6-mo treatment duration is based on observational data from our center, where patients typically receive treatment for 6 mo or 1 yr (2 or 4 infusion cycles, administered in 3-mo intervals aligning with the physiological cycle of bone turnover). In consultation with representatives of the Dutch CNO patient association, it was agreed that 6 mo period of potential placebo treatment was acceptable if followed by the open-label extension. Therefore, the 6-mo randomized phase is followed by a 6-mo open-label phase.

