### Outcomes and statistical analyses

The primary outcome of this trial is score of maximal pain on BPI (numerical rating scale 0-10) measured at the end of the 6-mo randomized phase. We will compare the difference between groups by generalized linear mixed model (GLMM) with analysis of covariance (ANCOVA) to account for baseline scores. The primary analysis will be intention-to-treat (see Table 1 and Figure 2). Secondary outcomes include a range of patient-reported,^32^^-^^40^ biochemical, and radiological outcomes, as well as their intercorrelation, baseline factors associated with treatment response,^41^^,^^42^ and cost-effectiveness^43^ (see Table 1 for measurement instruments, statistical analyses, and timepoints). Sensitivity analyses include a per-protocol and an as-treated analysis of the primary outcome. Missing data on the outcomes not evaluated by GLMM are imputed and handled through maximum likelihood techniques. No interim analyses are conducted.

**Table 1 TB1:** Primary and secondary outcomes of the PAM-CNO trial.

	**Outcome**	**Instrument**	**Timepoint of collection**	**Statistical analysis**	**Timepoint of analysis**
**Primary**	Score for maximal pain at CNO lesion sites	BPI	0, 3, 6, 9 and 12 mo	GLMM with ANCOVA	6 mo
**Secondary**	Score for minimal, average, and activity-related pain at CNO lesion sites	BPI	0, 3, 6, 9 and 12 mo	GLMM with ANCOVA	6 and 12 mo
**PROMs**	Shoulder function	SFA			
		SRQ			
	General health	SF-36			
	Quality of Life	EQ-5D			
	Work activity	Work Activity Score			
	Physical activity	IPAQ			
	Fatigue	MVI-20			
	Patient global	PGIC			
	Burden of a relative	Carer-QoL			
	Pain diary	NRS 0-10 for pain	2 d per wk, for entire 1-yr trial span	GLMM	6 and 12 mo
	Achievement of mild pain, as defined by ≤4/10 for maximal pain on BPI	BPI	0, 3, 6, 9, and 12 mo	Chi-square between groups, reported as odds ratio with 95% confidence interval	3, 6, and 12 mo
	Achievement of ≥50% reduction in maximal pain on BPI	BPI	0, 3, 6, 9, and 12 mo		
	% of patients with reduction in standard dose of NSAIDs/COXIBs	-	3, 6, and 12 mo		
**Biochemical**	ESR, CRP	Standard laboratory evaluation	0, 3, 6, 9, and 12 mo	GLMM with ANCOVA	6 and 12 mo
	Pro- and anti-inflammatory cytokines	ELISA			
	Bone markers	ELISA			
	mRNA expression	MLPA	0, 6, and 12 mo		
	T-lymphocyte counts	FACS			

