**Radiological**	Progression or regression of either sclerosis, hyperostosis, erosions, ankylosis, or soft tissue calcification	[^18^F]NaF-PET/CT	0, 6, and 12 mo	Chi-square between groups, reported as odds ratio with 95% confidence interval	6 and 12 mo
	Quantitative isotope uptake in CNO-lesions by SUV_max_			GLMM with ANCOVA	6 and 12 mo
**Correlations**	SUV_max_ with maximal and average pain	[^18^F]NaF-PET/CT and BPI	0, 6, and 12 mo	Pearson’s R or Spearman’s Rho as appropriate	0, 6, and 12 mo
	SUV_max_ with ESR and CRP	[^18^F]NaF-PET/CT and standard laboratory evaluation	0, 6, and 12 mo		
**Predictors of treatment response**	Diagnostic delay (yr)	-	0 mo	GLMM in pamidronate group, with maximal pain score on BPI as outcome	6 mo
	Baseline lesional isotope uptake (SUV_max_)	[^18^F]NaF-PET/CT	0 mo		
	Degree of central sensitization	CSI	0, 6, and 12 mo		
	Degree of neuropathic pain	PAIN-DETECT	0, 6, and 12 mo		
	Baseline presence of erosions, hyperostosis, and/or ankylosis	[^18^F]NaF-PET/CT	0 mo		
	Baseline presence of elevated ESR and/or CRP	-	0 mo		
**Cost-effectiveness**	Trial-based cost-utility from a societal perspective in accordance with the Dutch health-economics guidelines	IPCQ	0, 3, 6, 9, and 12 mo	Trial-based cost-utility analysis with costs-per-quality adjusted life yr, based on net-benefit analysis and friction-cost method.	6 and 12 mo (extrapolated to life-long discounted time horizon)

Abbreviations: ANCOVA; Analysis of Covariance, [18F]NaF-PET/CT; Sodium-fluoride positron emission tomography, BPI; Brief Pain Inventory, CarerQoL; Care-related Quality of Life Instrument, CNO; Chronic Nonbacterial Osteitis, COXIBs; Cyclooxygenase 2 Inhibitors, CSI; Central Sensitization Inventory, FACS; Fluorescence Activated Cell Sorting, ELISA; enzyme-linked immunosorbent assay, EQ-5D; EuroQol 5-Dimension, ESR; Erythrocyte Sedimentation Rate; GLMM; Generalized Linear Mixed Model, IPAQ; International Physical Activity Questionnaire, MLPA; Multiplex Ligation-dependent Probe Amplification, MVI-20; Multidimensional Fatigue Inventory-20, NRS; Numerical Rating Scale, NSAIDs; Non-Steroidal Anti-Inflammatory Drugs, PGIC; Patient Global Impression of Change, SF-36; Short Form Health Survey, SRQ; Shoulder Rating Questionnaire, SUV_max_; Standardized Maximum Uptake Value.

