### Sample size

Based on our observational data on adult CNO patients with a maximum pain score of ≥6/10 treated with intravenous pamidronate, BPI score for maximal pain is expected to decrease from a mean of 8 with standard deviation (±) of 2 to a mean of 6 ± 2 in the active treatment arm. In rheumatoid arthritis, the placebo effect on pain has been estimated at 16-22 at a 100-mm scale.^44^ However, because evidence-based treatments for CNO are entirely lacking—potentially reducing patient confidence in any given treatment—and many patients present with advanced disease due to diagnostic delays, we anticipate a smaller effect in the placebo arm of this trial, with pain levels decreasing from 8 ± 2 to 7.5 ± 2. We use a power of 80% and an alpha of 0.05. As the primary analysis is done with ANCOVA, adjustment for correlation between baseline and follow-up scores was done (Pearson’s correlation coefficient calculated at 0.479), with a required sample size of 35 patients per arm (total *n* = 70).^45^ In case of screen failure or drop-out before the 6-mo primary endpoint, patients will be replaced to meet the required sample of 70.

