A third challenge encountered in this trial was the choice for the primary outcome of patient-reported pain. Ideally, we would use a composite score that includes patient-reported outcomes such as pain and objective measures of inflammatory activity, reflecting both patient relevance and the biological mechanisms of treatment. However, for CNO, no objective markers of inflammatory activity are currently proven. Systemic inflammation markers are suboptimal indicators of disease activity due to their frequently normal levels at diagnosis,^2^ and the same holds for radiologic signs of disease activity such as increased isotope uptake, since it has been shown to persist despite evident clinical improvement, which may prompt overtreatment.^49^ Consequently, we use patient-reported pain at the site of CNO bone lesions as the primary outcome of this trial. While this is most relevant for patients, it may be modulated via different mechanisms which may complicate interpretation of the results. Therefore, patients are clearly instructed to differentiate and score the nociceptive inflammatory bone pain.^53^ Additionally, neuropathic and nociplastic pain are measured with standardized questionnaires to explore their association with treatment response. Recognizing that radiologic signs of disease activity in CNO need to be further investigated, this trial includes quantified uptake on [^18^F]NaF-PET/CT in the secondary analyses. This imaging modality is sensitive for bone pathology and yields quantitative parameters of bone turnover, which have shown to be elevated in CNO lesions and correlate with ESR.^46^ The longitudinal data on quantified [^18^F]NaF uptake from this trial will further elucidate the working mechanism of pamidronate, revealing whether pamidronate can quantitatively reduce bone turnover, and whether a decrease is associated with a reduction in pain.

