A final essential consideration of the PAM-CNO trial will be whether its results will be applicable to the pediatric CNO population as well. From a clinical perspective, there are similar observational data supporting the use of pamidronate in pediatric CNO, and this trial may reinforce the clinical body of evidence.^25^^,^^54^ From a pathophysiological perspective, it appears that adult and pediatric CNO may share common auto-inflammatory mechanisms, which may lend further credence to the use of pamidronate in both age groups.^55^ Therefore, results of the PAM-CNO trial may extrapolate to pediatric CNO, especially since bisphosphonates have shown to be safe and well-tolerated in children too.^56^

In conclusion, this first RCT on the effectiveness of pamidronate in adult patients with CNO is expected to have a significant impact, as there is currently no established treatment for this rare condition. Should pamidronate be found effective for pain control, future research should explore the optimal dosage and treatment schedule, and identify specific patient subgroups which may benefit the most. Also, pamidronate should be compared against TNFi which is commonly also used as second-line treatment in adult CNO. Additionally, this study will provide useful information on whether quantified [^18^F]NaF uptake can serve as an indicator of disease activity and treatment response in adult CNO. If the data support this idea, subsequent studies may consider this parameter when developing composite scores for disease activity in adult CNO.

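### Predictors of treatment response are modelled in the pamidronate arm only, so the analysis cannot distinguish factors that predict pain under either allocation from factors that predict benefit from pamidronate

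*Protocol article*

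**What the plan says.** The Objectives section states the aim: "Additional objectives are to evaluate baseline predictors of treatment response". The Introduction, in the paragraph after Figure 1, gives as one reason for adequately powered trials the need to "identify predictors of therapy response". The section on outcomes and statistical analyses lists "baseline factors associated with treatment response" among the secondary outcomes. The Discussion says that neuropathic and nociplastic pain are measured "to explore their association with treatment response".

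Table 1 names six factors: diagnostic delay, baseline lesional SUVmax, central sensitisation, neuropathic pain, baseline structural damage, and elevated ESR and/or CRP. It gives one method for all of them, "GLMM in pamidronate group, with maximal pain score on BPI as outcome", with analysis at 6 months. Nothing in the article plans an arm-by-factor interaction or uses the placebo arm for this aim.

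**The concern.** Response to a treatment is a contrast: what happens on the drug compared with what would have happened without it. The planned model has no such contrast. A factor that goes with more pain at 6 months whatever the allocation will appear in it as a predictor of poor response. Central sensitisation is an obvious candidate. The error can also run the other way: a factor that truly changes the drug effect can be hidden if its prognostic effect has the opposite sign.

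The article's own reasoning makes this matter. It justifies placebo control because the "primary outcome is patient-reported pain, which is susceptible to a placebo-effect". The predictor analysis uses that same outcome and drops the control. What is at stake is the interpretation of a stated objective: readers may take the results as showing which patients gain from pamidronate when the model does not address that.

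This is not a detail left to an analysis plan. Table 1 fixes the population, the outcome and the timepoint.

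**Working it through.** **Inputs from the article (Sample size section).** 35 per arm; SD 2; baseline to follow-up correlation 0.479; pamidronate arm expected to "decrease from a mean of 8 with standard deviation (±) of 2 to a mean of 6 ± 2"; placebo arm from 8 to 7.5. The expected difference is therefore 2.0 − 0.5 = 1.5 points. Two-sided alpha of 0.05 is assumed.

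**The plan's own figure.** The predictor analysis has no stated sample size or power. For the primary analysis, the stated inputs give 2 × (1.96 + 0.84)² × 2² × (1 − 0.479²) / 1.5² ≈ 21.5, so 22 per arm and not 35. That is a separate matter. The 35 is used below as the planned number, and the argument does not depend on how it was reached.

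**Algebra.** Let 6-month pain be α + ρ·baseline + τ·arm + β·factor + γ·(arm × factor) + error. Here β is prognosis and γ is modification of the drug effect.
- Slope in the pamidronate arm: β + γ.
- Slope in the placebo arm: β.
- Difference between the slopes: γ.

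The planned model estimates β + γ. Predicting benefit requires γ, and only the placebo arm supplies β.

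**How much of the treated-arm change is not drug effect.** On the article's figures, 0.5 / 2.0 = 25%. With the placebo response that it cites from rheumatoid arthritis (16 to 22 on a 100-mm scale, or 1.6 to 2.2 points), it would be 1.6 / 2.0 = 80% to 2.2 / 2.0 = 110%.

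**Simulation 1: purely prognostic factor (γ = 0), independent of baseline pain.** 6,000 trials per row, 35 per arm. The correlations are assumptions; the article gives none. Entries are the percentage of trials with p < 0.05.

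| Correlation with 6-month pain | One arm, no baseline term | One arm, baseline-adjusted | Interaction, both arms |
|---|---|---|---|
| 0.2 | 21 | 26 | 5 |
| 0.3 | 43 | 52 | 5 |
| 0.4 | 67 | 79 | 5 |
| 0.5 | 89 | 95 | 5 |

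**Simulation 2: factor that acts only through baseline pain.** At correlations of 0.2, 0.3 and 0.4, the one-arm model without baseline flags it in 21%, 43% and 68% of trials. With baseline adjustment the rate is about 5% throughout.

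**Simulation 3: true modifier** (slopes in BPI points per SD of the factor, residual SD 2 × √(1 − 0.479²) = 1.76, baseline-adjusted).
- β = +0.8, γ = −0.8: the one-arm slope averages 0.00 with 5% rejection, so the modifier is missed. The interaction estimate averages −0.79, with 43% power.
- β = 0, γ = −0.8: the one-arm slope averages −0.80 with 71% rejection. The slope equals the modification here, but one arm's data cannot show that β is zero.

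**Cost in precision.** The simulated standard error is about 0.44 for the interaction and 0.31 for the one-arm slope, a ratio of about 1.4. The smallest modification detectable with 80% power is about (1.96 + 0.84) × 1.76 × √(2/35) ≈ 1.18 points per SD. For a binary factor split 50:50 it is about (1.96 + 0.84) × 1.76 × √(4/17.5) ≈ 2.35 points.

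**The case against.** **A descriptive reading is available.** The article speaks in places of association with response, and Table 1 openly says that the model is fitted in the pamidronate group. Which treated patients end with less pain is a legitimate exploratory question. This stands, but then the block heading and the objective promise more than the model gives, and relabelling is still needed.

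**The percentages are not the plan's error rate.** They are the ordinary power to detect a real association; the error lies in reading that association as differential benefit. They also depend on the model form. Table 1 does not list the covariates of the GLMM, which an article may leave to the full protocol. If baseline pain is included, patients who merely start with more pain are largely dealt with, as simulation 2 shows. This stands as a limit on the size. It does not rescue the analysis for prognostic effects beyond baseline pain.

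**The remedy is weak at this sample size.** The detectable modification of about 1.2 points per SD compares with a whole planned drug effect of 1.5. True, but low power for the right quantity is no reason to estimate a different one.

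**Stronger readings that the article does not support.** A reader might infer that the one-arm model finds only prognostic factors. It does not: its slope mixes prognosis and modification, and equals the modification when prognosis is nil. A reader might also take the Discussion's phrase "identify specific patient subgroups which may benefit the most" as an aim of this trial. That sentence assigns the task to future research, conditional on pamidronate proving effective, so it does not bear on the point. Nor does the article say that predictor results will be used to select or exclude patients.

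**Conclusion.** The point holds, with moderate severity. The algebra needs no assumption about effect sizes: as fixed in Table 1, the analysis cannot separate prognosis from modification of the pamidronate effect. The size rests on assumed correlations, a single continuous factor, linear effects and full data on 35 per arm. On those terms a purely prognostic factor is flagged in roughly 20% to 95% of trials, falling to about 5% if it works only through baseline pain and the model adjusts for that.

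The defect concerns an additional objective. The 6-month intention-to-treat comparison, the sample size and the between-arm secondary analyses do not depend on it, so it would be wrong to infer that the trial's main conclusion is at risk.

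**What to change.** Replace the method in the predictor block with a 6-month BPI maximal pain model in both randomised arms, containing baseline BPI, arm, the factor and the arm-by-factor interaction. Use the value of each factor at 0 months; Table 1 also collects the central sensitisation and neuropathic pain questionnaires at 6 and 12 months, so this should be said explicitly. Report each interaction with its 95% CI, labelled exploratory.

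If the pamidronate-only model is kept, beside the interaction or in place of it, label it as prognostic factors for pain under pamidronate and word the objective to match.

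The cost is wording and a few lines of code. Table 1 does not restrict collection of these factors to one arm, so no new data are needed. The price is precision: intervals about 1.4 times wider. The report should say that a null interaction is not evidence of no modification.

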### Eligibility criteria

Patients ≥18 yr of age with an established diagnosis of CNO are the population base of this study. In the absence of validated classification criteria for CNO, the primary diagnostic criterion is sterile bone inflammation at one or more skeletal sites in the anterior chest wall, with or without involvement of other skeletal sites. This is identified based on clinical features (inflammatory bone pain and possibly signs of inflammation on physical exam), biochemical markers (mild to moderate increase in inflammation markers, though often these are within normal range), and imaging findings (bone marrow edema, sclerosis, hyperostosis, erosions, ligament ossification, ankylosis of joints, and increased isotope uptake on nuclear imaging). If a bone biopsy is performed, histopathology compatible with sterile bone inflammation includes nonspecific inflammation and increased bone turnover. Sterile bone inflammation, and herewith diagnosis of CNO, is confirmed through a multidisciplinary, integrated assessment. Of note, this definition of sterile bone inflammation/CNO means that patients can have varying skeletal distribution patterns and may or may not have additional (extra)skeletal features such as arthritis, enthesitis, sacroiliitis, palmoplantar pustulosis, psoriasis, or severe acne.

Further inclusion criteria are as follows:

Score for maximal pain (concerning bone pain at lesion sites over the past week) ≥6/10 as measured by Brief Pain Inventory (BPI).^30^Insufficient response to at least one NSAID/COXIB at maximum approved and tolerated dosage, intolerance or contraindication to these agents, or indication for direct second-line treatment due to active vertebral lesions.A washout period of prior bisphosphonates (6 mo since last administration).

Exclusion criteria are as follows:

<18 yr of age.Active pregnancy wish, active pregnancy, or nursing.Generalized pain without pain at the site of CNO lesions.Bisphosphonate allergy.Estimated glomerular filtration rate < 30 ml/min.Uncontrolled endocrine comorbidities, active cancer (treatment), or other severe comorbidity preventing the attendance of study visits.Severe language barrier preventing the completion of questionnaires.Mental disability.

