For imaging evaluation, we selected sodium fluoride positron emission tomography ([^18^F]NaF-PET/CT), because it offers several advantages compared with other common techniques such as magnetic resonance imaging (MRI) and bone scintigraphy using technetium-99 m radio-labeled hydroxymethylene diphosphonate ([^99^mTc]Tc-HDP). [^18^F]NaF-PET/CT offers a higher spatial resolution and is therefore more sensitive than MRI to visualize structural features such as sclerosis and hyperostosis, especially in the region of anterior chest wall.^29^ Compared with [^99^mTc]Tc-HDP, [^18^F]NaF-PET/CT allows for shorter scanning time lower radiation exposure. Finally, [^18^F]NaF-PET/CT provides quantitative data on bone turnover that correlate with clinical disease activity in other metabolic bone diseases. We recently demonstrated that these quantitative data can be generated for CNO as well and may candidate as disease activity imaging biomarkers.^46^^-^^48^ Quantitative [^18^F]NaF-PET/CT data may be preferred over other imaging biomarkers, such as [^99^mTc]Tc-HDP-based isotope uptake, which has been shown to have an imprinting pattern.^49^ Additionally, it may be favored over bone marrow edema detection on MRI, as edema cannot be adequately detected or quantified in sclerotic bone.^50^ [^18^F]NaF-PET/CT is performed at 0, 6, and 12 mo, using a 5-ring Discovery MI PET/CT machine (GE Healthcare, Chicago, IL, USA). Data are acquired ~30 min after intravenous Na18F administration at a dose of around 1-MBq/kg body weight. A single experienced nuclear physician and radiologist assess all [^18^F]NaF-PET/CT scans using a standardized reporting format, with consensus-based assessment in cases of disagreement.^5^^,^^46^ Each potential lesion site is evaluated for sclerosis, hyperostosis, erosions, ankylosis, and [^18^F]NaF-uptake. Quantitative [^18^F]NaF-uptake is determined by drawing volumes of interest in CNO lesions and reference bone identified by CT.

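### The inflammation predictor in Table 1 cuts ESR and CRP to elevated or not, although both are measured numerically and analysed as values elsewhere in the same table

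*Protocol article*

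**What the plan says.** The Objectives section places baseline predictors of treatment response among the additional objectives. Table 1, in Outcomes and statistical analyses, gives six predictor rows and one method for them: "GLMM in pamidronate group, with maximal pain score on BPI as outcome". Four rows are quantities: diagnostic delay in years, baseline SUVmax, degree of central sensitization and degree of neuropathic pain. Two are presence items: "Baseline presence of elevated ESR and/or CRP" and "Baseline presence of erosions, hyperostosis, and/or ankylosis".

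Elsewhere in Table 1, ESR and CRP are treated as numbers. The biochemical block analyses them by GLMM with ANCOVA at 6 and 12 months, and the correlation block lists "SUV_max_ with ESR and CRP", using Pearson's or Spearman's coefficient.

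On how the markers behave, Eligibility criteria describes a "mild to moderate increase in inflammation markers, though often these are within normal range". The Discussion calls them suboptimal indicators of disease activity "due to their frequently normal levels at diagnosis".

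**The concern.** When a numeric marker is reduced to elevated or normal, every patient on the same side of the cut is treated as identical. If many patients are in the normal range, most of the ordering among them is lost, and the few elevated patients carry the whole contrast. In a single-arm analysis of about 35 patients there is little information to spare. A marker that truly predicts response could then be reported as unrelated to it. Nothing in the data collection forces the cut, because the values are recorded and used in other rows of the same table.

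**Working it through.** **Inputs from the article.** 35 patients per arm and alpha 0.05 (Sample size); analysis in the pamidronate group (Table 1).

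**The plan's own figure.** The article states no power or precision for the predictor analysis. Its only relevant figure is 35 per arm, which was set for the primary outcome. A check from the stated inputs (difference 7.5 − 6 = 1.5, SD 2, correlation 0.479) runs as follows:

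- ANCOVA SD = 2 × √(1 − 0.479²) = 1.756
- n = 2 × (1.96 + 0.84)² × 1.756² / 1.5² ≈ 22 per arm (23 with a t-based calculation)

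So 35 does not follow from those inputs. That is a separate matter, on the conservative side. Here 35 is simply taken as the planned number of pamidronate patients.

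**Assumptions.** Two-sided test (the article does not state sidedness). One marker roughly normal, for example after taking logs, and linearly related to 6-month pain. Share elevated between 10% and 50%, since the article says only that values are often or frequently normal.

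**Step 1: information kept by a cut.** With a proportion p elevated, the share kept is φ(z_p)² / [p(1 − p)], where φ is the standard normal density at the cut.

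- p = 0.5: 0.399² / 0.25 = 0.637
- p = 0.3: 0.348² / 0.21 = 0.576
- p = 0.2: 0.280² / 0.16 = 0.490
- p = 0.1: 0.1755² / 0.09 = 0.342

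Effective n is 35 times the share kept.

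**Step 2: power.** The cut shrinks a true correlation r to r × √(share kept). Power is Φ[atanh(r) × √(35 − 3) − 1.96]. For r = 0.45 kept continuous: 0.485 × 5.657 − 1.96 = 0.78, so power is 78%. With an even split, r becomes 0.45 × √0.637 = 0.359, giving 0.376 × 5.657 − 1.96 = 0.17 and power 57%.

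| Share elevated | Information kept | Information lost | Effective n | Power, r = 0.45 | Power, r = 0.30 |
|---|---|---|---|---|---|
| not cut | 100% | 0% | 35 | 78% | 42% |
| 50% | 64% | 36% | 22 | 57% | 28% |
| 30% | 58% | 42% | 20 | 52% | 26% |
| 20% | 49% | 51% | 17 | 45% | 23% |
| 10% | 34% | 66% | 12 | 33% | 17% |

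**Step 3: the joint flag.** If the row means one flag that is positive when either marker is elevated, the loss was simulated for two normal markers with correlation 0.3 to 0.9, each elevated in 10% to 50% of patients. It is 38% to 63% relative to using the mean of the two markers, and 41% to 76% if only one marker drives pain.

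**Step 4: the structural row, for comparison.** Suppose that row is one any-of flag and k of 35 patients are negative. The difference detectable at 80% power is 2.80 × 1.756 × √(1/k + 1/(35 − k)). This gives 3.0 BPI points for k = 3, 2.1 for k = 7 and 1.7 for an even split. The result turns on k, for which the article gives no basis.

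**The case against.** **A table label is not a coding rule.** The rows are a few words in a condensed article. The and/or may mean that ESR and CRP are entered separately, and an analysis plan that is not shown may define the coding. This has force against reading the row as a single joint flag. It does not remove the point: even if entered separately, each marker is still described as elevated or not.

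**The loss depends on linearity.** If what matters is inflamed versus not inflamed, variation within the normal range carries little signal and the cut costs less. This stands, and it is why the figures are conditional. The article gives no argument for a threshold effect, and it uses the values numerically in other rows.

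**Small numbers are the main limit.** At a true correlation of 0.30, power is 42% even without a cut. That is fair: keeping the values does not make the analysis well powered. It only avoids a further avoidable loss.

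**A reader might infer that about half the information is lost.** That figure corresponds to a single marker elevated in about 20% of patients, a share the article does not give.

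**A reader might also infer that the structural flag hardly varies and that graded data stand ready to replace it.** The documents do not support this. Eligibility criteria lists seven imaging findings and requires none of the three in the flag. Sample size says only that "many patients present with advanced disease due to diagnostic delays", without a frequency. Trial workplan and data collection states that "Each potential lesion site is evaluated for sclerosis, hyperostosis, erosions, ankylosis, and [^18^F]NaF-uptake", but describes no severity grade. A count of affected sites would measure extent of disease, which is a different question from whether damage is present.

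**Conclusion.** The point holds for ESR and CRP. Table 1 dichotomises two markers whose values are recorded and used numerically elsewhere in the same table, in an analysis of about 35 patients. Under a linear relation on a roughly normal scale, a single-marker cut loses about 36% of the information at best (an even split) and about 66% if 10% are elevated. Power at a true correlation of 0.45 falls from 78% to between 57% and 33%. Within that model some loss occurs at any prevalence; only its size depends on the unstated share.

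For the structural row nothing is established. If an any-of flag is meant and nearly all patients are positive, the contrast would be imprecise, but the article gives neither a prevalence nor a grading.

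Priority is low. The analysis serves an additional, exploratory objective and the primary result is untouched.

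**What to change.** In the predictor block of Table 1, or in the analysis plan before the code is broken, replace the elevated ESR and/or CRP row by two continuous predictors: baseline log-CRP and baseline ESR. Keep the elevated/normal flag as a descriptive summary. No change to the structural row is requested.

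No new data are needed, since both markers are already measured at baseline. The cost is one extra coefficient (seven predictors instead of six, with ESR and CRP likely to be correlated) and an effect expressed per unit or per log unit rather than as a yes/no contrast.
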